
##### Executive functions

For executive functions, we will include three executive cognitive processes based on the work of Miyake and colleagues [43] and frequency of inclusion in clinical batteries [38]: 1) response inhibition, 2) set shifting; and 3) working memory. Response inhibition involves deliberately inhibiting dominant, automatic, or prepotent responses. Set shifting requires one to go back and forth between multiple tasks or mental sets [43]. Working memory involves monitoring incoming information for relevance to the task at hand and then appropriately updating the informational content by replacing old, no longer relevant information with new incoming information. We will assess: 1) response inhibition using the Stroop Colour-Word Test [44], 2) set shifting using the Trail Making Test (Parts A & B) [45]; and 3) working memory using the Digit Symbol Substitution Test (DSST; 90 s) [46].

##### Balance and mobility

The Short Physical Performance Battery (SPPB) [47] will be used to capture domains of strength, gait speed and balance, by performing standing balance, walking and sit-to-stand exercises. The SPPB is scored out of 4 points per component and has a maximum score of 12. Low scores on the SPPB reflect poor performance.

##### Cardiovascular capacity

The Six Minute Walk Test (6-MWT) [48] will be used to measure cardiovascular capacity. This test asks participants to walk as far as they can (meters) in six minutes (breaks allowed). Before and after the walk, the participants’ blood pressure will be measured. The participants will be asked to rate their walk on the Borg Rating of Perceived Exertion [33]. The score on the 6-MWT is the distance (in meters) covered during six minutes.

##### Physical activity level

To obtain information about their physical activity, the Physical Activity Scale for the Elderly (PASE) [49, 50] will be administered. This 12-item questionnaire assesses the amount of time spent per day in the previous week on leisure activity time (light, moderate and strenuous activities), household work, and time spent volunteering.

##### Magnetic resonance imaging

Prior research has demonstrated that significant changes in brain volume can be observed after 32 h of computer-based cognitive training over a span of 8 weeks among older adults with subjective memory complaints [30] – a population very similar to ours. Thus, we will include neuroimaging outcomes in our proof-of-concept RCT. Our neuroimaging outcomes will include: 1) hippocampal volume and cortical thickness as determined by structural MRI; and 2) functional connectivity as determined by resting state functional MRI and seed-based approach. If interested and eligible, a subset of participants will be asked to do one MRI scan before and one after the completion of the 8-week training. Participants will be asked to come to the UBC for 1.5 h each visit. The scanning protocol will take approximately 50 min, and a series of anatomical scans will be performed in addition to a resting-state functional MRI scan.

Acquired structural and functional neuroimaging data will be analyzed using different pipelines. The Freesurfer image analysis suite [51] will be used for structural data analysis. Freesurfer is developed at the Martinos Center for Biomedical Imaging by Laboratory for Computational Neuroimaging (http://surfer.nmr.mgh.harvard.edu/). Data processing will include skull-stripping [52], motion correction [53], Talairach transformation [54, 55], atlas registration [56] and brain parcellation [55, 57]. The data will be manually checked, and if necessary corrected. Functional connectivity analysis will be using resting-state functional MRI (rsfMRI) data to investigate the effect of CCT (alone and preceding a 15-min walk) on functional connectivity. Resting-state fMRI data will be preprocessed using FSL (FMRIB’s Software Library). Data processing will include skull-stripping using Brain Extraction Tool (BET), motion correction using MCFLIRT, and spatial smoothing. Data will be manually checked, and if necessary corrected. Model-free independent component analysis (ICA) will be performed using FSL-MELODIC to examine whole-brain connectivity patterns, and with selecting independent resting-state components, we will look at between group differences. Seed-based functional connectivity analysis (SBA) will be performed to look at the correlations between regions of interest within and between networks. Connectivity maps will be created to show connections with the seed region (i.e., region of interest).

### Participant timeline

Eligible participants will attend a 1-hour information session at either the UBC or at VGH. During this one-hour information session, the study coordinator will give a short presentation that provides the potential participants with important details of the study. In addition, the potential participants will receive a copy of the consent form during this visit. Once written consent is obtained, a research assistant will schedule a baseline assessment. After completion of their baseline assessment, participants will be randomized into one of 3 training groups (i.e., FBT, Ex-FBT, or BAT). Following the 8-week intervention, participants will attend the final assessment session(s). For a complete timeline, see Fig. 2.

**Fig. 2 Fig2:**
[figure not shown]
Participant timeline

### Sample size and randomization

The required sample size for this study is calculated based on changes in the RAVLT (retention score). Specifically, we predict a mean change of 0.31 for the FBT group, a mean change of 0.40 for the Ex-FBT group, and a mean change of −0.31 for the BAT group. We made these estimates based on the work of Diamond and colleagues [58]. With a pooled standard deviation of 1.1, and alpha of 0.05, we will need 36 participants for a power of 0.80. To accommodate for a 10% drop-out rate, our total sample size comes to 120 participants (i.e., 40 FBT, 40 Ex-FBT, and 40 BAT).

Participants will be randomly allocated (1:1:1) to FBT, Ex-FBT, or BAT. The randomization sequence will be generated by an independent member of the team using computer software (www.randomization.com). Blocked randomization will be used, with a block size of 12. The group allocation will be concealed for the study coordinator. After enrolment, performed by a research assistant, and completion of the baseline assessment, the study coordinator will send a list of participant identification numbers to the independent member responsible for the randomization. This independent member will provide the study coordinator with the group assignment for the enrolled participants. After completion of baseline assessment at VGH, the participants will be informed of their group assignment. Outcome assessors will be blinded after treatment allocation.

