#### Primary outcome: Episodic memory

Our primary cognitive outcome will be (verbal) episodic memory as measured by the Rey Auditory Verbal Learning Test (RAVLT) [38]. The RAVLT is a valid, reliable, and widely used instrument of (verbal) episodic memory. Notably, a 2013 prospective study showed that among a combination of neuropsychological, neuroimaging, and cerebrospinal fluid markers, RAVLT performance was the best individual predictor of MCI conversion to dementia [39]. For the RAVLT, a list of 15 common words (List A) will be read to participants five times. Immediately after each time, they will be asked to recall as many words as possible. After the fifth trial, an interference list (List B) will be presented, after which participants will be asked to spontaneously recall the words form the original list (List A). Then, participants will be asked to spontaneously recall the original words (List A) after a 20-min delay (i.e., long delay free recall), and finally, they will be asked to circle words from the original list (List A) in a paragraph of text containing thirty underlined words (i.e., words from the original list plus distractor words). Scores will be calculated as the total number of words recalled: 1) across the five trials (total acquisition); 2) after the interference list (recall after interference); 3) on the fifth trial minus after the interference (loss after interference); 4) at recognition (number of words correctly identified from list A); and 5) after the 20-min delay (long delay free recall – our primary RAVLT measure of interest). We will focus on changes in memory (trial completion minus baseline) over the course of the study.

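### The sample size rests on an undefined RAVLT retention score, so the stated 80% power is not shown to apply to the primary measure, long delay free recall

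*Protocol article*

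**What the plan says.** Two sections of the protocol article bear on this.

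- **Primary outcome: Episodic memory.** The instrument is fixed: "Our primary cognitive outcome will be (verbal) episodic memory as measured by the Rey Auditory Verbal Learning Test (RAVLT". Five scores are then numbered. The first two are "across the five trials (total acquisition); 2) after the interference list (recall after interference", the next two are "on the fifth trial minus after the interference (loss after interference); 4) at recognition (number of words correctly identified from list A", and the fifth is the number of words recalled "after the 20-min delay (long delay free recall – our primary RAVLT measure of interest". The quantity of interest is the change: "We will focus on changes in memory (trial completion minus baseline) over the course of the study".
- **Sample size and randomization.** "The required sample size for this study is calculated based on changes in the RAVLT (retention score". The inputs follow: "we predict a mean change of 0.31 for the FBT group", 0.40 for Ex-FBT and −0.31 for BAT, attributed to one cited study, with a pooled SD of 1.1 and alpha of 0.05. The section concludes that 36 participants give a power of 0.80, and that a 10% drop-out allowance brings the total to 120, or 40 per arm.

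The Statistical analysis section plans two main contrasts in change: FBT versus BAT, and Ex-FBT versus BAT.

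**The concern.** The score used to size the trial and the score named as primary carry different names, and nothing in the article links them. None of the five listed scores is called a retention score, and the term is not explained. The inputs are given without units, so a reader cannot tell from the numbers whether they are words recalled after 20 minutes.

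The mean changes and SD are the article's only justification for 120 participants. If they describe long delay free recall, the power statement concerns the endpoint that will be tested. If they describe some other score, the primary endpoint has no stated effect, SD or power. As written, the reader cannot tell which case holds.

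**Working it through.** **Step 1. Compare the names.** The primary-outcome section lists total acquisition, recall after interference, loss after interference, recognition, and long delay free recall, the last being primary. The sample-size section uses a retention score. It matches none of the five by name, and no sentence equates it with any of them.

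**Step 2. Inputs, all from the sample-size section.** Mean changes are 0.31 (FBT), 0.40 (Ex-FBT) and −0.31 (BAT), with SD 1.1 and alpha 0.05. I take 36 as per arm, because 36 / 0.9 = 40 per arm and 3 × 40 = 120, which matches the stated total. Sidedness is not stated; I assume two-sided.

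**Step 3. Try to reproduce 36 per arm and 0.80.** For two means, n per arm = 2 (SD / difference)² (1.960 + 0.842)².

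- Ex-FBT versus BAT: difference 0.40 + 0.31 = 0.71, so n = 2 (1.1 / 0.71)² × 7.849 = 37.7, i.e. 38 per arm. This is close to the stated 36.
- FBT versus BAT: difference 0.31 + 0.31 = 0.62, so n = 2 (1.1 / 0.62)² × 7.849 = 49.4, i.e. 50 per arm.

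The stated size is therefore approximately that for the larger contrast only.

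**Step 4. Power at 36 per arm on the protocol's own inputs.** The standard error of a difference is 1.1 × √(2/36) = 0.2593. The noncentrality is 0.62 / 0.2593 = 2.39 for FBT versus BAT and 0.71 / 0.2593 = 2.74 for Ex-FBT versus BAT.

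| Method (two-sided 0.05) | FBT vs BAT | Ex-FBT vs BAT |
|---|---|---|
| Normal approximation | 0.667 | 0.782 |
| t, SD pooled over three arms (105 df) | 0.659 | 0.774 |
| t, two arms only (70 df) | 0.655 | 0.771 |

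Rounded, this is about 66% and 77%. The overall three-group F test at 36 per arm has noncentrality 36 × 0.2989 / 1.21 = 8.89 and power 0.753. Here 0.2989 is the sum of squared deviations of the three means from their average, 0.1333.

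**Step 5. What can be said about long delay free recall.** The article gives neither an expected change nor an SD under that name, so its power cannot be computed. Only the detectable difference in SD units can be stated. Under the normal approximation it is √(2/36) × 2.802 = 0.66 SD for 80% power, and with the t distribution it is 0.67 SD.

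**Step 6. Illustration only.** Hold the difference at 0.62 and assume an SD of change. Two-arm t power for FBT versus BAT is then 41% at SD 1.5, 25% at 2.0, 18% at 2.5 and 14% at 3.0. No section of the article supports these SDs. Holding the difference fixed is also arbitrary, since a different score would have its own expected difference. These figures show sensitivity and do not estimate the trial's power.

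**The case against.** The strongest reply is that retention score may simply be a loose label for recall after the 20-minute delay. The article does not define the term and the cited study is not at hand, so this cannot be excluded. In that case the inputs do belong to the primary measure.

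This reply stands, and it limits the point. A reader might infer that the inputs definitely describe another variable and that the stated power does not apply to the primary endpoint. That depends on a definition of retention as a difference or ratio between recall trials, which the article does not give. A reader might also take the falling power in Step 6 as the cost of the mismatch. It is not, because if the true difference on long delay free recall is larger, power is higher.

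It is also fair to say that the primary measure is stated unambiguously, that the model and contrasts are fixed whatever the sizing label, and that this is a proof-of-concept trial. An estimate and interval for long delay free recall would be valid and interpretable regardless.

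The reply does not remove the need to edit. The conflict lies between two things the article does state, so it cannot be put down to detail left to a fuller document. Even if the label is only loose, Step 4 shows that 0.80 is not what 36 per arm delivers for both planned contrasts.

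**Conclusion.** The point holds in this form: the article sizes the trial on an undefined score that is absent from its own list of RAVLT scores, so the 80% power is not shown to apply to long delay free recall. That is weaker than saying it does not apply, which the document cannot establish.

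The size depends on which reading is true. If the inputs are for long delay free recall, power at 36 per arm is about 66% for FBT versus BAT and 77% for Ex-FBT versus BAT. This assumes two-sided 0.05, SD 1.1, a simple comparison of changes and no multiplicity adjustment. That shortfall comes from the inputs and not from the label, but it means that relabelling alone would leave the figure wrong. If the inputs are for another score, power for the primary endpoint is unknown, and only the detectable difference of about 0.67 SD can be given.

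The analysis is not biased under either reading. What is affected is the stated justification for the sample size.

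**What to change.** Use one score name in the primary-outcome and sample-size sections.

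- **If the inputs are for long delay free recall:** replace the retention label with that name, state that the inputs are in words recalled, and restate the power that 36 evaluable per arm gives for each planned contrast (about 66% and 77% on the present inputs).
- **If they are not:** define the retention score, then give the expected change and SD of change for long delay free recall with their source. Report the resulting power at 36 per arm, or failing that the difference detectable with 80% power (about 0.67 SD).

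The cost is one recalculation and a few amended sentences. No extra participants are needed. The downside is that the stated power may fall below 0.80 and would have to be reported as such.

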### Statistical analysis

#### Effects of CCT

The primary and secondary outcomes will be analyzed using an identical analytic model, which will follow the intention-to-treat principle, such that all randomized participants will be included to estimate treatment effects irrespective of deviations from treatment protocol (e.g., loss to follow-up, non-compliance). This will be done using linear mixed models using maximum likelihood estimation. The model will include random intercepts, and fixed effects of time (baseline, trial completion), intervention assignment (FBT, Ex-FBT, BAT), and their interaction. Baseline MoCA score and age will also be included as fixed effect covariates. Treatment effects will be indicated by a statistically significant treatment by time interaction. Two planned simple contrasts will be performed to assess differences in changes in the primary and secondary outcomes between: 1) the FBT group and the BAT group; and 2) the ex-FBT group and the BAT group. A secondary planned contrast will determine whether FBT and ex-FBT will differ in changes in the primary and secondary outcomes over time. To explore maintenance of treatment effects, we will perform repeated measures with linear mixed models using maximum likelihood estimation. The models will include random intercepts, and fixed effects of time (baseline, trial completion, 1-year follow up), intervention assignment, and their interaction. Baseline MoCA score and age will also be included as fixed effect covariates.

Follow-up sensitivity analyses will restrict the study sample to individuals with valid data at all three time points (baseline, trial completion, and 1-year follow-up). The same linear mixed models describe above will be employed to determine whether inferences will be similar for the intention-to-treat and complete-case study samples.

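### The stated 80% power at 36 per arm does not follow from the protocol's own inputs: it is about 66% for FBT vs BAT, 77% for Ex-FBT vs BAT and 75% for the interaction test

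*Protocol article*

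**What the plan says.** The section on sample size and randomization sizes the trial on change in the RAVLT. Its predicted mean changes are gains of 0.31 in the FBT arm and 0.40 in the Ex-FBT arm, and a loss of 0.31 in the BAT arm. It then concludes: "With a pooled standard deviation of 1.1, and alpha of 0.05, we will need 36 participants for a power of 0.80". A 10% dropout allowance brings the total to 120, or 40 per arm. The section does not say which comparison the 0.80 belongs to, whether the test is one- or two-sided, or that 36 is a per-arm number.

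The tests are named under Effects of CCT. A treatment effect is to be shown by a significant interaction of arm and time, which has 2 degrees of freedom with three arms and two time points. In addition, "Two planned simple contrasts will be performed to assess differences in changes in the primary and secondary outcomes": FBT against BAT, and Ex-FBT against BAT. FBT against Ex-FBT is a secondary contrast.

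**The concern.** The article prints every input to the calculation together with a result, so the result can be checked, and it does not follow from the inputs. The first aim is to compare FBT, and also Ex-FBT, with BAT. A reader will take 80% as the chance that the trial detects the assumed effects. If the true figure for FBT is about 66%, the chance of missing the assumed effect is about 34%, against the 20% implied.

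A mixed result would also be easy to misread. The two active arms are assumed to differ by only 0.40 − 0.31 = 0.09, yet the chance that exactly one of the two contrasts is significant is considerable (shown in the working). A significant Ex-FBT result beside a non-significant FBT result could then be taken to mean that the walk made the difference.

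**Working it through.** **Inputs, all from the sample size section.** Mean changes 0.31, 0.40 and −0.31; SD 1.1, read as the SD of change because the means are changes; alpha 0.05, taken as two-sided without multiplicity adjustment; 36 evaluable per arm.

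**The plan's own figures.** The dropout step reproduces: 36/0.9 = 40 per arm and 108/0.9 = 120. This also shows that 36 is per arm. Read as a total (12 per arm), it would give only 29% power for the overall test. The 0.80 does not reproduce, as follows.

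**Two-arm contrasts.** Standardized difference d = difference/1.1; noncentrality = difference/(1.1 × √(2/36)) = difference/0.2593.

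- FBT vs BAT: difference 0.31 + 0.31 = 0.62; d = 0.564; noncentrality 2.391. By the normal approximation, power = Φ(2.391 − 1.960) = 66.7%. The t test gives 65.5% (70 df) or 65.9% (105 df, three-arm variance).
- Ex-FBT vs BAT: difference 0.40 + 0.31 = 0.71; d = 0.645; noncentrality 2.738. Normal approximation: Φ(2.738 − 1.960) = 78.2%. The t test gives 77.1% (70 df) or 77.4% (105 df).

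**Overall interaction (2 df).** The grand mean is 0.40/3 = 0.133. The squared deviations are 0.0312, 0.0711 and 0.1965, which sum to 0.2989. Hence f = √(0.2989/3)/1.1 = 0.287 and λ = 36 × 0.2989/1.21 = 8.89. The noncentral F test with 2 and 105 df gives 75.3%; the chi-square version gives 76.5%.

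| Test (two-sided 0.05) | Power at 36 per arm | Power at 40 per arm | Per arm for 80% |
|---|---|---|---|
| FBT vs BAT (t) | 65.5% | 70.2% | 51 |
| Ex-FBT vs BAT (t) | 77.1% | 81.4% | 39 |
| 2-df interaction (F) | 75.3% | 79.98% | 41 |

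The column for 40 per arm assumes no dropout at all, although the plan treats 40 as already absorbing 10%.

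**Other routes to 36.** One-sided t tests need 40 per arm for FBT vs BAT and 31 for Ex-FBT vs BAT, so neither gives 36. The mean of the two active arms (difference 0.665), compared one-sided with BAT as if two equal groups of 36, gives 81.5% and would need 34 to 35 per group. That comes close, but no such test is planned.

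**Both contrasts together.** In a simulation at 36 per arm, both contrasts were significant in 57.2% of trials and at least one in 86.0%. Exactly one was therefore significant in 86.0 − 57.2 = 28.8%. Ex-FBT alone accounts for 77.4 − 57.2 = 20.2 points of this, and FBT alone for 65.9 − 57.2 = 8.7, which agrees up to rounding.

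**Sensitivity to rounding at 36 per arm.** An SD printed as 1.1 may lie between 1.05 and 1.15.

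| SD | FBT vs BAT | Ex-FBT vs BAT | Interaction |
|---|---|---|---|
| 1.05 | 69.5% | 80.8% | 79.3% |
| 1.10 | 65.5% | 77.1% | 75.3% |
| 1.15 | 61.6% | 73.3% | 71.2% |

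With the means also at the favourable edge of their rounding (0.315, 0.405, −0.315) and SD 1.05, the figures are 70.9%, 81.8% and 80.6%.

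**If 1.1 were the SD of a single score.** Then the SD of change = 1.1 × √(2(1 − ρ)), where ρ is the pre-post correlation. FBT vs BAT reaches 80% at 36 per arm only if the SD of change is at most 0.926, so ρ must be at least 1 − (0.926/1.1)²/2 = 0.65.

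**Detectable difference.** At 36 per arm, SD 1.1 and 80% power, the t test detects 0.737, or about 0.74. Both assumed differences (0.62 and 0.71) are smaller.

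**The case against.** The best counter-argument is that only one of the three shortfalls is secure. The SD is given to one decimal. At 1.06, Ex-FBT vs BAT reaches 80%, and with favourable rounding of both SD and means the interaction test does too. The normal approximation puts Ex-FBT vs BAT at 78.2% with 38 per arm, close to the plan's 36. The section also never says that 80% applies to FBT vs BAT, so the largest gap belongs to a test for which the figure was not expressly claimed. Finally, this is a proof-of-concept trial reported in a condensed article, and the SD might not be that of change.

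Much of this stands as a qualification. The Ex-FBT gap is marginal, and both it and the interaction gap depend on the unrounded SD, though rounding could equally make them worse. The Discussion and abstract say only what positive results would mean, so misreading of a null FBT result is a risk, not something the plan commits to.

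The objection does not save the sentence. FBT vs BAT is part of the first aim and the first planned contrast, and it stays near 71% at best. An unnamed comparison does not help when none of the named ones gives 80% at the printed values. A single-score SD would need a correlation that is nowhere stated. A proof-of-concept label can justify modest power but not a misstated figure. Condensation explains missing detail, whereas here the inputs and result are both printed and disagree.

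**Conclusion.** The concern holds. At the printed inputs, 36 evaluable per arm gives about 66% power for FBT vs BAT, 77% for Ex-FBT vs BAT and 75% for the interaction that defines a treatment effect, against a stated 80%. The conclusion is firm for FBT vs BAT under any rounding of the inputs. For the other two it holds at the printed values, but the gap is 3 to 5 points and could close or widen with the unrounded SD. All of this assumes that 1.1 is the SD of change, two-sided alpha of 0.05, no multiplicity adjustment and 10% dropout. Because the plan claims a power that its design does not have for a main comparison, the statement has to be corrected.

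**What to change.** Keep N = 120 and replace the power sentence with something like: *With 36 evaluable participants per arm (40 randomized, 10% dropout), an SD of change of 1.1 and two-sided alpha of 0.05, power is 66% for FBT vs BAT, 77% for Ex-FBT vs BAT and 75% for the 2-df treatment-by-time test; the difference detectable with 80% power is 0.74.*

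Before this is adopted, the sponsor should state whether 1.1 is the SD of change and give its unrounded value. If it is a single-score SD, the assumed pre-post correlation must be stated and the three powers recalculated. Any gain claimed from adjusting for the baseline score needs the same correlation.

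The cost is wording only: no extra participants and no change to conduct, but a less favourable stated power. For comparison, truly reaching 80% after 10% dropout would take 46 per arm (41/0.9; 138 in total) for the interaction test, or 57 per arm (51/0.9; 171 in total) for FBT vs BAT.

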The objective of the current proof-of-concept RCT will be to examine the effect of CCT, alone and preceded by a 15-min brisk walk, on cognitive function and to explore the underlying neural mechanism in community dwelling older adults. Therefore, our aim is four-fold: 1) To compare the effects of an 8-week CCT program (i.e., Fit Brains***®*** Training: FBT), as well as the effects of a 15-min brisk walk prior to FBT (i.e., Ex-FBT), with an active control (i.e., Balanced And Toned, BAT) on cognitive performance in older adults aged 65–85 years old; 2) Using structural and functional Magnetic Resonance Imaging (MRI), to explore the effect of FBT and Ex-FBT compared with BAT on brain structure and function; 3) To explore whether the effects of FBT and Ex-FBT are moderated by baseline cognitive status (i.e., Mild Cognitive Impairment (MCI) versus non-MCI); 4) To explore whether Ex-FBT has additional benefits compared with FBT; and 5) To explore whether potential benefits from CCT are maintained at 1-year follow-up.

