#### Baseline cognitive status as a moderator

To determine whether treatment effects are similar for individuals identified as having MCI, we will add MCI status as an additional fixed effect in the linear mixed models described above. Moderation will be indicated by a statistically significant MCI status by treatment by time interaction. In the presence of moderation, the planned contrasts described above will be re-computed after stratifying by MCI status. This will identify how MCI status moderated the effects of treatment on the outcome of interest.

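### MCI status, the only effect moderator the protocol names, is known before allocation but is not used to stratify it, so its balance across arms is left to chance: a cheap improvement, not an error

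*Protocol article*

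**What the plan says.** The aims at the end of the Background include: "To explore whether the effects of FBT and Ex-FBT are moderated by baseline cognitive status". The section on baseline cognitive status as a moderator tests this with an interaction of MCI status, treatment and time. If that interaction is significant, "the planned contrasts described above will be re-computed after stratifying by MCI status". No other effect moderator is named.

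Eligibility admits people with and without MCI: it requires an MMSE of at least 24, sets no MoCA bound, and excludes MCI only where certain causes are suspected. The section on classification by baseline cognitive status calls a MoCA of 26 or below probable MCI. The section on global cognitive function instead puts MCI at scores below 26.

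On timing, the participant timeline says: "After completion of their baseline assessment, participants will be randomized into one of 3 training groups". The section on sample size and randomization gives a 1:1:1 ratio, 40 per arm, and: "Blocked randomization will be used, with a block size of 12". For the handover, "the study coordinator will send a list of participant identification numbers to the independent member responsible for the randomization". No stratum is mentioned. The statistical analysis section enters baseline MoCA and age as fixed-effect covariates and lists no interaction of either with time.

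**The concern.** The classification that the moderation aim depends on is available when allocation takes place, and an independent team member already receives a list from which groups are assigned. Leaving MCI status off that list means its share in each arm is decided by chance. Two things could suffer. The moderation contrast loses precision when the MCI counts in two arms are unequal, and an MCI cell in one arm could become small. If change in episodic memory also differs by MCI status, chance imbalance adds noise to the main contrasts, because the planned covariate does not address it.

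**Working it through.** **Inputs from the protocol.** Three arms of 40; SD 1.1, read here as the SD of change; planned FBT−BAT difference 0.31 − (−0.31) = 0.62. The arm size follows from the stated 36 and 10% dropout: 36/0.9 = 40, and 3 × 40 = 120. Only the arm size, the SD and the 0.62 are used below.

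**Assumption.** The MCI share is not given. Shares of 25%, 40% and 50% are used, that is M = 30, 48 and 60 of 120.

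**Step 1: spread of the MCI count.** 120 is ten full blocks of 12, so one list gives exactly 40 per arm. If MCI status is unrelated to place on the list, the count in an arm is hypergeometric with variance M × (1/3)(2/3) × (120 − M)/119. The three counts sum to M, so the difference between two arms has three times that variance.

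| MCI share | Variance per arm | SD of the difference between two arms |
|---|---|---|
| 25% | 5.04 | 3.89 |
| 40% | 6.45 | 4.40 |
| 50% | 6.72 | 4.49 |

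**Step 2: chance of a 15-point gap.** Fifteen points of 40 is 6 people. For one contrast, the normal approximation with continuity correction uses z = 5.5/SD: 1.41, 1.25 and 1.22, giving two-sided chances of 16%, 21% and 22%. By simulation, the chance that FBT or Ex-FBT differs from BAT by 6 or more is 27%, 35% and 36%.

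**Step 3: cost to the moderation contrast.** With a and b MCI participants in FBT and BAT, the variance of the MCI-by-treatment contrast in change is 1.1² × [1/a + 1/b + 1/(40 − a) + 1/(40 − b)].

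- A 15-point gap at a 25% share, 7 against 13: the bracket is 0.1429 + 0.0769 + 0.0303 + 0.0370 = 0.2871, against 2(1/10 + 1/30) = 0.2667 under balance. SE ratio √(0.2871/0.2667) = 1.04.
- The same gap at a 50% share, 17 against 23: 0.2046 against 0.2000. SE ratio 1.01.
- Over all allocations, mean SE inflation is about 2% at 25% and 1% at 40% and 50%. The 95th percentile is about 11%, 5% and 3%.
- An MCI cell of 5 or fewer occurs in about 6% of allocations at 25% and essentially never at 40% or 50%.

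**Step 4: what balance cannot repair.** With perfect balance the SE is 1.1 × √0.2667 = 0.568 at 25% and 1.1 × √0.2000 = 0.492 at 50%. Power for an interaction as large as 0.62 is Φ(0.62/SE − 1.96), that is 0.19 and 0.24.

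**Step 5: the main contrasts.** A MoCA main effect adds the same amount at baseline and at trial completion, so it cancels from change and hardly touches the treatment-by-time estimate. Suppose, generously, that MCI and non-MCI participants differ in change by 0.62. A 15-point gap then shifts FBT−BAT by 0.15 × 0.62 = 0.09, against a standard error of 1.1 × √(2/40) = 0.25. The share of variance due to MCI is p(1 − p) × 0.62²/1.1²: 6% at p = 0.25 and 8% at p = 0.50, or 3–4% of the SE. If the difference in change is 0.3, it is under 2% of the variance.

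**Step 6: effect of the remedy.** With blocks of 12 kept separately within MCI classes, the largest between-arm gap in MCI count has median 1, 95th percentile 3 and maximum 4. Without strata, over shares of 20–70%, the median is 4–5 and the 95th percentile 8–11.

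**The case against.** The strongest reply is that nothing here is wrong. Unstratified permuted blocks give a valid test, ordinary standard errors already allow for chance imbalance, and the protocol never promises balance on MCI. The aim is exploratory in a proof-of-concept trial, and within-class contrasts follow only a significant interaction. The moderation model conditions on MCI status, so unequal shares cost it precision but do not bias it. The average loss is 1–2% of a standard error, and the small-cell risk appears only towards the low end of the assumed range. All of this stands, and it limits how much weight the point can carry.

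The baseline MoCA covariate is a weaker defence. Without a MoCA-by-time term it adjusts level and not change (step 5). It also cannot enlarge a small cell.

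Nor is condensation of the article a full answer. The section describes the ratio, the software, the block size and what is sent for allocation, and names no stratum.

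A reader might infer that the main contrasts are biased, or that the moderation aim fails because allocation is unstratified. The documents support neither. Randomization protects the main contrasts on average, and the moderation test is limited mainly by a total of 120.

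**Conclusion.** The point holds as a modest, inexpensive design improvement. The only moderator the protocol names is known before allocation and is not balanced by it. For MCI shares of 25–50%, a gap of 15 points or more from BAT in at least one active arm has a chance of 27–36%, or 16–22% for a single contrast. The typical cost to the moderation contrast is 1–2% of its standard error, reaching about 11% in the worst 5% of allocations at a 25% share. The effect on the main contrasts is small even under a generous assumption about how MCI affects change.

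These figures rest on the assumed share, on 40 analysed per arm, and on MCI status being unrelated to place on the list. It would go too far to conclude that stratifying secures the moderation aim: it balances MCI across arms but does not set the overall share, and power for an interaction of 0.62 stays near 0.2 even under perfect balance.

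**What to change.** Stratify allocation by baseline MoCA class. First reconcile the two cut-offs (26 or below, against below 26), so that one definition serves both the stratum and the moderator. The coordinator adds the class to the list of identification numbers. The independent member keeps two blocked lists with concealed block sizes, for example a mix of 6 and 12. Blocks of 3 should be avoided because they make allocation more predictable. Include the stratum and its interaction with time in the linear mixed model.

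The cost is a second list, one extra column, and scoring the MoCA before allocation. Arms or class groups may end slightly unequal. A partly filled block of 12 can hold at most 4 of one arm, so each list can leave a gap of at most 4, and the two lists together at most 8. If allocation has already begun, stratify the remaining cohorts and report MCI counts by arm.
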